Appendix 4 Intervention Guidelines in the Event of Anemia

The use of erythropoietin (NeoRecormon) ≥3000 IE 3 times week sc initially in the event of anemia is permitted throughout the study at the discretion of the treating physician with the exception if the patient has any of the following exclusion criteria for the use of erythropoietin: platelet count >500,000, risk of thrombosis, or poorly controlled hypertension, especially if hemoglobin decreases persistently to < 10.0 g/dL or in the event of a rapid decrease in hemoglobin exceeding 4.0 g/dL over a 2 week period. If erythropoietin is initiated, a new ribavirin concentration at local lab should be evaluated after 4 weeks in Groups A (“Loading”) and B (“Priming”).

In the event of anemia, dose reductions of ribavirin are permitted in all study arms throughout the study at the discretion of the treating physician.

If hemoglobin decreases to < 8.0 g/dL, ribavirin should be discontinued.

If hemoglobin decreases to < 7.0 g/dL, blood transfusion should be considered at the discretion of the treating physician.

If hemoglobin decreases to < 6.5 g/dL, blood transfusion should be given.

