### Ribavirin Dose Modifications

If the ribavirin concentration measured on day 28 in Groups A and B is below the target concentration (2.5 mg/L (10.25 mol/L)), the dose of ribavirin should be increased as soon as possible preferably within 2 weeks of measuring the ribavirin concentration if the patient can tolerate an increase. The new recommended dose is the previously given dose divided by the concentration of ribavirin measured multiplied by the target concentration (2.5 mg/L (10.25 mol/L)) (see Appendix 3).In the event of a change in ribavirin dosing in Groups A (“Loading”) and B (“Priming”), a new local ribavirin concentration should be evaluated after 4 weeks. Ribavirin should be administered twice-daily with food.

Where dose reduction is required stepwise incremental adjustments of 200 mg (1 tablet) should be utilized where clinical circumstance allows.

If either of the following is confirmed, it is recommended that the ribavirin dose should be reduced, at the discretion of the investigator dependent on local treatment guidelines:

- A patient without significant cardiovascular disease experiences a fall in hemoglobin to <10 g/dL (<100 g/L) and >8.5 g/dL (>85 g/L) or
- A patient with stable cardiovascular disease experiences a fall in hemoglobin by >2 g/dL (>20 g/L) during any 4 weeks of treatment

For the purposes of this protocol, patients with “stable cardiovascular disease” include not only patients with known, stable cardiac and vascular disorders, but also patients with major cardiac risk factors including hypertension and diabetes mellitus.

Patients who have more than a 3 g/dL (30 g/L) decrease from baseline in their Hgb concentration should have an appropriate work-up for anemia, including reticulocyte count, search for sources of bleeding, etc.

Moreover, ribavirin should be discontinued under the following circumstances:

- If a patient without significant cardiovascular disease experiences a fall in hemoglobin confirmed to be less than 8.0 g/dL (80 g/L).
- If a patient with stable cardiovascular disease maintains a hemoglobin value <12 g/dL (<120 g/L) despite 4 weeks on a reduced dose of 600 mg.

Ribavirin monotherapy is not allowed; in the event that PEG-IFN alfa-2a treatment has to be permanently discontinued the patient must cease all study medications and must be followed for safety reasons for at least 12 weeks.

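### The ribavirin stop rules for anaemia disagree: Section 8.3.2 has a confirmed-value stop and a separate cardiovascular stop, yet a flat stop below 8.0 g/dL appears there and in three other places

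*Protocol*

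**What the plan says.** Section 8.3.2 (Ribavirin Dose Modifications) lists two circumstances for stopping ribavirin, divided by cardiovascular status.

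- No significant cardiovascular disease: "If a patient without significant cardiovascular disease experiences a fall in hemoglobin confirmed to be less than 8.0 g/dL (80 g/L").
- Stable cardiovascular disease: the patient "maintains a hemoglobin value <12 g/dL (<120 g/L) despite 4 weeks on a reduced dose of 600 mg".

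The second group is defined broadly. It covers known stable cardiac and vascular disorders "but also patients with major cardiac risk factors including hypertension and diabetes mellitus". The group also has its own trigger for a dose reduction: "A patient with stable cardiovascular disease experiences a fall in hemoglobin by >2 g/dL (>20 g/L) during any 4 weeks of treatment". Section 8.3.2 presents the reduction triggers as recommendations that the investigator may apply at discretion.

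Further down, Section 8.3.2 gives a rule with neither qualifier: "If hemoglobin decreases to < 8.0 g/dL, ribavirin should be discontinued". The identical sentence is in Appendix 4 (the anaemia intervention guideline), in Section 5.3.2 (Safety Assessments) and in the safety row of the synopsis. On dose reduction, those three places say only that "dose reductions of ribavirin are permitted in all study arms throughout the study at the discretion of the treating physician". None of the three has a cardiovascular branch, a confirmation step or a reference to Section 8.3.2.

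**The concern.** A site handling a low haemoglobin would naturally turn to Appendix 4, because its title says that is its purpose. There it finds neither the cardiovascular stop nor the confirmation step. A site that reads Section 8.3.2 finds both, and then a sentence in the same section that ignores them.

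The patients concerned can be enrolled. Section 4.3 excludes severe cardiac disease but not hypertension or diabetes as such, and it leaves coronary and cerebrovascular disease to the investigator's judgment. Entry haemoglobin can be as low as 12 g/dL in women and 13 g/dL in men, close to the 12 g/dL in the cardiovascular stop.

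Section 8.5.2.3 calls anaemia the primary toxicity of ribavirin, and Group A takes a double dose for its first two weeks. Anaemia grade by arm is a safety variable (Section 9.1.3). The per-protocol set requires at least 80% of planned Copegus (Section 9.2.1.1). In an open-label multicentre trial, sites that follow different texts could stop ribavirin at different points. That would affect exposure, the anaemia comparison and per-protocol membership.

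**Working it through.** There is no figure in the plan to reproduce. The check sets the five statements side by side and applies them to four situations.

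**What each place contains**

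| Place | Stop below 8.0 g/dL | Confirmation required | Cardiovascular stop | Reference to 8.3.2 |
|---|---|---|---|---|
| Section 8.3.2, stop bullets | Only without significant cardiovascular disease | Yes | Yes: below 12 g/dL despite 4 weeks on 600 mg | (same section) |
| Section 8.3.2, later sentence | All patients | No | Not repeated | (same section) |
| Section 5.3.2 | All patients | No | No | No |
| Synopsis, safety row | All patients | No | No | No |
| Appendix 4 | All patients | No | No | No |

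**What each text does for a given patient**

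1. No cardiovascular disease, confirmed value below 8.0 g/dL. Every text stops ribavirin, so there is no conflict.
2. No cardiovascular disease, unconfirmed value below 8.0 g/dL. The 8.3.2 bullet does not yet stop, because it needs a value "experiences a fall in hemoglobin confirmed to be less than 8.0 g/dL (80 g/L"). The later sentence in 8.3.2, Section 5.3.2, the synopsis and Appendix 4 all stop.
3. Stable cardiovascular disease, value below 8.0 g/dL, not yet 4 weeks on 600 mg. Neither 8.3.2 bullet applies: the first is for patients without significant cardiovascular disease, and the second needs the 4 weeks. The flat sentence stops ribavirin in all four places where it stands.
4. Stable cardiovascular disease, value from 8.0 to below 12 g/dL after 4 weeks on 600 mg. The second 8.3.2 bullet stops. Section 5.3.2, the synopsis and Appendix 4 contain no stop for this patient.

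**Where each difference lies.** Situations 2 and 3 already arise inside Section 8.3.2, between its bullets and its later sentence. Only situation 4 depends on whether the site reads Section 8.3.2 or one of the three shorter texts.

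**The case against.** The case for leaving the text alone has several parts.

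- **The rules can be combined.** A flat stop below 8.0 g/dL for everyone, with the cardiovascular stop added, is a coherent reading. Appendix 4 never says that a cardiovascular patient must stay on ribavirin between 8.0 and 12 g/dL. This reading would settle situations 3 and 4, but the protocol does not state it. It does not settle situation 2, where one text waits for confirmation and the others do not.
- **Sites are told where to look.** Section 7.1 refers to Section 8.3 for ribavirin adjustment, and Section 8.5.2.3 says to stop therapy if cardiovascular status deteriorates. Both points stand and narrow the problem. Neither is in Appendix 4, and Section 8.3 holds both versions of the stop.
- **The cardiovascular stop is narrow.** It needs 4 weeks at 600 mg. Appendix 3 starting doses after any loading are 800 to 1400 mg, and reductions go in 200 mg steps where circumstances allow, so a patient reduced only to 800 or 1000 mg does not meet it. This stands.
- **Dose reduction is discretionary everywhere.** This also stands. Appendix 4 omits a recommended trigger, not a mandatory one.

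A reader might go further in two ways that the documents do not support. One is to treat this as Appendix 4 departing from a consistent Section 8.3.2. It is not, because that section carries the same flat sentence. The other is to size the gap as 12 − 8.0 = 4.0 g/dL, or to compare a fall of 13.0 − 8.0 = 5.0 g/dL from the male entry minimum with the 4 g/dL fall in Section 4.3. The first compares a conditional stop with an immediate one. The second compares a total fall over any period with an eligibility judgment about tolerating an acute fall in coronary or cerebrovascular disease.

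**Conclusion.** The inconsistency is real and safety-related. The texts agree in one of the four situations and differ in three. The two clearest are the unconfirmed value below 8.0 g/dL, where they give different instructions, and the cardiovascular patient at 8.0 to below 12 g/dL after 4 weeks on 600 mg, whose stop is missing from the anaemia guideline.

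Situation 3 assumes that a patient classed as having stable cardiovascular disease is not also counted as being without significant cardiovascular disease. The protocol does not relate the two terms.

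No numerical size can be given. The number of enrolled patients in the cardiovascular group is not stated, nor how many would reach 600 mg, so any effect on the anaemia comparison, the per-protocol set or SVR is possible but cannot be estimated. Nothing here shows an error in the primary viral-kinetic analysis. The point is worth correcting because it concerns the main toxicity of the study drug and is cheap to fix.

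**What to change.** Reconcile the synopsis, Section 5.3.2, both parts of Section 8.3.2 and Appendix 4 into one agreed set of anaemia rules, kept in one place. It should state:

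- whether a low value must be confirmed before ribavirin is stopped;
- how the cardiovascular rules and the all-patient stop apply together, including for a cardiovascular patient who has not completed 4 weeks on 600 mg;
- how the terms significant and stable cardiovascular disease relate.

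Replace every other copy with a cross-reference. The repeated sentence inside Section 8.3.2 must be included: matching the shorter texts to that section as it stands would leave its two parts in disagreement. Which rule stands is for the sponsor's clinicians.

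The cost is a wording amendment, submitted as the protocol's section on modifications requires. It needs no new visits, tests or patients.

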Appendix 5 Instructions for Sample Processing and Shipment for RibaC:

**Please note that all samples should be collected using PPT VacutainerâTube before the morning dose of ribavirin because we will be monitoring ribavirin concentrations throughout the study!**

1. **Virology: HCV-RNA (screening visit, day 0 (just prior to the 1st dose of pegylated interferon; day 0 is the day that the first dose of the study medication is given), day 3, day 7 (before the 2nd dose of pegylated interferon), day 28 (before the 5th dose of pegylated interferon), week 12, End of Treatment, Follow-Up week 24)**

**Use PPT VacutainerTube (6ml) BD product:**

- - - - - Draw the tube and immediately mix sample by gentle inversion 10 times; DO NOT SHAKE
        - After mixing, store the PPT tube upright at room temperature until centrifugation
        - Centrifuge the PPT tube at 1100 x g for 10 minutes, swing-out bucket rotor. Blood samples should be centrifuged within two (2) hours of blood collection
        - After centrifugation transfer the tube to the designated local storage laboratory containing a –70°C freezer (if this is not possible use a –20°C freezer)
        - At the storage laboratory transfer the plasma from each PPT tube into three 1 ml tubes.
        - Label the 1 ml tubes
        - Store in –70°C freezer until shipment (if this is not possible store at –20°C)
        - **Please note:** **Samples from screening visit, day 28, week 12, week 24, End of Treatment, and Follow-Up week 24 will also be sent at room temperature to a local laboratory using Roche COBAS TaqMan for HCV-RNA quantification.**

# Shipment

- - - - - Check that labels are in place
        - Place frozen samples in polypropylene container and close it
        - Place polypropylene container into a BioPack
        - Place BioPack into the dry ice in thermal transport box; dry ice should surround the BioPack
        - Send to Department of Virology Göteborg, Sweden upon completion of the study

1. **Parmacokinetics at central lab: Trough concentration of ribavirin (day 1, day 3, day 7, day 28, week 8, week 12, and end-of-treatment) obtained before the morning dose of ribavirin. Please note that for Groups A and B an additional plasma sample will be obtained on day 28 for analysis of ribavirin concentration at a local lab, and if the target concentration is not met, an increase in ribavirin dose in accordance with appendix 3 is recommended, but not mandatory at the discretion of the treating physician. In the event of a change in ribavirin dosing in Groups A (“Loading”) and B (“Priming”), a new local ribavirin concentration should be evaluated after 4 weeks.**

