## Secondary Objectives

To prospectively evaluate:

- the efficacy of 2 week loading or 4 week priming followed by concentration targeted dosing of ribavirin in combination with peginterferon alpha-2a in interferon naïve patients with chronic hepatitis C (CHC) virus genotype 1 infection as compared to standard-of-care dosing of ribavirin in combination with peginterferon alpha-2a as evaluated by the proportion of patients achieving VRVR ( “very rapid virologic response” i.e. HCV-RNA below 1000 U/mL at treatment day 7 after intiation of PEG-interferon), RVR (“rapid virologic response”, undetectable HCV-RNA at treatment day 28 after intiation of PEG-interferon), cEVR (“complete early virologic response”, i.e. undetectable HCV-RNA at treatment week 12 after intiation of PEG-interferon), and pEVR (“partial early virologic response”, i.e. decline of HCV-RNA by at least 2 log10 compared with baseline at treatment week 12 after intiation of PEG-interferon).
- the efficacy of 2 week loading or 4 week priming followed by concentration targeted dosing of ribavirin in combination with peginterferon alpha-2a in interferon naïve patients with chronic hepatitis C (CHC) virus genotype 1 infection is superior to standard-of-care dosing of ribavirin, peginterferon alpha-2a therapy as evaluated by sustained virological response (SVR, undetectable HCV-RNA 24 weeks after end of treatment).
- the predictive value of monitoring of viral load at day 0 (before the 1st dose of peginterferon alpha-2a), day 3, day 7 (before the 2nd dose of peginterferon alpha-2a), and day 28 (before the 5th dose of peginterferon alpha-2a) for determining which patients will obtain a sustained virological response (SVR) when treated with ribavirin and peginterferon alpha-2a therapy.
- the association between the trough concentrations of ribavirin (day 1, day 3, day 7, day 28, week 8, week 12, week 16, and end-of-treatment), and the therapeutic efficacy of ribavirin and peginterferon alpha-2a therapy.
- The association between plasma IP-10 (days 0, 1, 3, 7, and 14, and weeks 8, 18, and 24), and the therapeutic efficacy of ribavirin and peginterferon alpha-2a therapy.
- the effect of IL-28B polymorfism on the viral kinetic response and SVR.
- the effect of baseline vitamin D concentrations on the viral kinetic response and SVR.

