# STUDY design

## Overview of Study Design and Dosing Regimen

This study will be conducted as a phase III, open label, multicenter trial. A total of 105 patients will be randomized to one of three possible treatment groups.

**Group A:** (“Loading”): PEG-IFN α-2a 180 g/week plus loading (≥26 mg/kg/day for 2 weeks followed by ≥13 mg/kg/day) and concentration targeted (≥ 2.5 mg/L (10.25 μmol/L) 28 days after initiation of ribavirin therapy) dosing of ribavirin and response guided treatment duration (RVR 24 weeks, non-RVR 48 weeks, pEVR consider 72 weeks), follow-up period 24 weeks.

**Group B**: (“Priming”): Standard-of-care dosing of ribavirin (≥13 mg/kg/day) without PEG-IFN for 4 weeks followed by 24-48 additional weeks of PEG-IFN α-2a 180 g/week plus standard-of-care dosing of ribavirin (≥13 mg/kg/day) and concentration targeted (≥ 2.5 mg/L (10.25 μmol/L) 28 days after initiation of ribavirin therapy) dosing of ribavirin and response guided treatment duration (RVR 28 weeks, non-RVR 52 weeks, pEVR consider 76 weeks), follow-up period 24 weeks.

**Group C:** (“Standard-of-Care”): PEG-IFN α-2a 180 g/week plus standard-of-care dosing of ribavirin (≥13 mg/kg/day without any measurement of ribavirin concentration) and response guided treatment duration (RVR 24 weeks, non-RVR 48 weeks, pEVR consider 72 weeks), follow-up period 24 weeks.

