**Ribavirin Plasma Concentration**

Trough plasma concentrations of ribavirin will be obtained before the morning dose of ribavirin day 1, day 3, day 7, day, 14, day 28, week 8, week 12, week 18, End-of-Treatment. Group B (“Priming”) will also obtain trough plasma sample for ribavirin day -27 (the first day after initiation of “priming” dose of ribavirin) and day -21 (one week after initiation of “priming” dose of ribavirin).

Instructions for sampling and shipment can be found in Appendix.

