## Statistical and Analytical Methods

### Analysis Plan

This is a pilot trial with the viral kinetic response and SVR measured as described above, during the first 12 weeks of therapy as primary endpoint with the aim of investigating the feasibility and safety of “loading” and “priming” dosing of ribavirin in conjunction with PEG-IFN for chronic HCV genotyp 1. Intention-to-treat and Per-protocol analysis on primary endpoints will be performed for patients receiving at least one dose of the study drugs. Additionally, an analysis of SVR with regards to whether or not the target concentration of ribavirin 2.5 mg/L (10.25 μmol/L) at day 28 was achieved across all study arms will be performed.

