**Appendix 3: COPEGUS Intended Dose and Dose Adjustment Guidelines**

| Group A: Intended Ribavirin Dosing | | |
| --- | --- | --- |
| Weight | Ribavirin dose day 0 – day 14* | Ribavirin dose day 15 -  End of Treatment** |
| 45-60 kg | 1600 mg | 800 mg |
| 61-75 kg | 2000 mg | 1000 mg |
| 76-90 kg | 2400 mg | 1200 mg |
| 91-105 kg | 2800 mg | 1400 mg |
| *Dose given TID. **Ribavirin concentration measured on treatment day 28. Dose | | |
| adjustments will be made at the discretion of the treating physician with the goal of | | |
| achieving ≥ 2.5 mg/L (10.25 μmol/L). A new ribavirin concentration is recommended | | |
| after an additional period of 4 weeks if the ribavirin dose is adjusted as above. | | |

| Group B and C: Intended Ribavirin Dosing |  |
| --- | --- |
| Weight | Ribavirin dose day 0 –  End of Treatment a,b |
| 45-60 kg | 800 mg |
| 61-75 kg | 1000 mg |
| 76-90 kg | 1200 mg |
| 91-105 kg | 1400 mg |
| aNo ribavirin concentrations will be measured while on treatment for group C.  bGroup B will receive 4 weeks of priming with ribavirin without PEG-IFN. | |

If the ribavirin concentration is below the target 2.5 mg/L (10.25 μmol/L) 28 days after the initiation of ribavirin, the dose of ribavirin should be increased as soon as possible preferably within 2 weeks of measuring the ribavirin concentration if the patient tolerates. The new recommended dose is the previously given dose divided by the concentration of ribavirin measured multiplied by the target concentration, i.e. 2.5 mg/L (10.25 μmol/L) as suggested in the table below. In the event of an increase in ribavirin dosing in Groups A (“Loading”) and B (“Priming”), a new local ribavirin concentration should be evaluated after 4 weeks.

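### The ribavirin trough lists disagree, the site sampling instructions being the shortest, and the Group C wording taken literally conflicts with the planned day-28 analysis in all arms

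*Protocol*

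**What the plan says.** **Trough times.** Section 5.3.1 (Ribavirin Plasma Concentration) sets pre-dose troughs at "day 1, day 3, day 7, day, 14, day 28, week 8, week 12, week 18, End-of-Treatment", with no arm excepted. It adds that Group B "will also obtain trough plasma sample for ribavirin day -27", and again on day -21. It then points to the appendix for sampling and shipment. The synopsis objective carries the same nine common time points.

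Section 2.2 states the same secondary objective, the association of trough concentration with efficacy, on a different list: "day 1, day 3, day 7, day 28, week 8, week 12, week 16, and end-of-treatment".

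Appendix 5, in its pharmacokinetics item, gives sites a third list: "Trough concentration of ribavirin (day 1, day 3, day 7, day 28, week 8, week 12, and end-of-treatment) obtained before the morning dose of ribavirin". It adds a further day-28 sample for the local laboratory in Groups A and B.

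**Group C.** The synopsis and Section 3.1 describe standard-of-care dosing "without any measurement of ribavirin concentration". A footnote in Appendix 3 says that no "ribavirin concentrations will be measured while on treatment for group C". Section 7.1 also describes Group C as having no day-28 assessment. Yet Section 9.2.1 and the synopsis plan an analysis of SVR by whether the target concentration "at day 28 was achieved across all study arms will be performed". Section 1.4.1 describes the control arm more softly, as one where levels are not to hand during treatment.

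**The concern.** A trough not drawn on the day cannot be drawn later. Appendix 5 is the text that tells site staff what to collect, and it is the shortest of the lists. It goes from day 7 to day 28, so Group A has no trough at the end of the 14-day loading period; the next one comes 14 days after loading stops. It also has no Group B trough during the priming weeks. What is at stake is the completeness of a stated secondary objective.

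The Group C wording is a separate matter. If a site took it literally, the control arm would have no concentrations and the planned day-28 analysis could not include it.

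**Working it through.** **Step 1: set the lists side by side.**

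| Source | Day 14 | Week 16 | Week 18 | Group B days -27, -21 | Common time points |
|---|---|---|---|---|---|
| Section 5.3.1 | yes | no | yes | yes | 9 |
| Synopsis objective | yes | no | yes | not listed | 9 |
| Section 2.2 | no | yes | no | not listed | 8 |
| Appendix 5 | no | no | no | no | 7 |

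All four contain days 1, 3, 7 and 28, weeks 8 and 12, and end of treatment. Section 5.3.1 minus Appendix 5 is day 14 and week 18 in every arm, plus days -27 and -21 in Group B. Appendix 5 adds nothing that Section 5.3.1 lacks. Week 16 appears only in Section 2.2.

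**Step 2: count scheduled troughs.** Section 3.2 gives 35 patients per arm, 105 in all. Assume full attendance and no early stopping.

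- Section 5.3.1: 105 × 9 + 35 × 2 = 945 + 70 = 1,015.
- Appendix 5: 105 × 7 = 735.
- Difference: 1,015 − 735 = 280, or 280/1,015 = 27.6%. Of these, 105 × 2 = 210 are day-14 and week-18 troughs and 35 × 2 = 70 are Group B priming troughs.

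**Step 3: what the missing days represent.** Group B starts ribavirin on day -28, so day -27 is 1 day and day -21 is 7 days after the first ribavirin dose. By time since first ribavirin dose they correspond to days 1 and 7 in Groups A and C. If days are counted from the first peginterferon dose, Group B's retained day-1 trough follows about four weeks of ribavirin.

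**Step 4: is there back-up plasma?** Appendix 5 schedules IP-10 plasma on day 14 and in week 18, in the same tube type and before the morning dose, split into three 1 ml aliquots. No draw listed there covers day -27 or -21.

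**Step 5: Group C, two readings.**

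- Never measured: the literal sense of the synopsis and Section 3.1. The day-28 analysis then has 70 patients in two arms.
- Measured centrally, with no result during therapy: Section 1.4.1 says this in substance. Appendix 3 limits its statement to the treatment period. Section 5.3.1 and Appendix 5 except no arm. Appendix 5 presents the local day-28 sample in Groups A and B as an extra one, and it ships the central samples at the end of the study. The analysis then has 105 patients in three arms.

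Only the second reading is compatible with Section 9.2.1.

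**The case against.** Appendix 5 is a handling and shipment appendix, and sites may time their draws from Section 5.3.1 or from the visit schedule in Section 5.1. The Section 5.1 tables could not be read in the text at hand and may list every draw. This stands as a limit on the likely loss, but it does not remove the contradiction between Sections 2.2 and 5.3.1 and Appendix 5.

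The 210 day-14 and week-18 troughs are not necessarily 210 lost specimens. The IP-10 aliquots might serve, and the week-12 stopping rule means that fewer than 105 patients may still be on treatment at week 18. Both points stand. Against the first, the IP-10 aliquots ship to a different laboratory from the ribavirin samples, and nothing assigns them to ribavirin assay.

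Several stronger readings are tempting, but the documents do not support them:

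- **Loading exposure is lost altogether.** Days 1, 3 and 7 all fall within loading and are kept. They are also the days named in the objective on predicting steady-state concentration.
- **Day 14 is the highest trough in Group A.** This needs a half-life that the protocol does not give. With a double dose for 14 days and simple first-order accumulation, the day-14 level relative to the later steady state is 2(1 − 2^(−14/t)). An assumed half-life t of 7 days gives 1.50, 12.5 days gives 1.08, and 14 days gives 1.00; longer values give less than 1. Doses may also be raised after day 28.
- **The early-exposure rationale fails without days -27 and -21.** Section 1.4.1 speaks of the first day of combination therapy, and Group B's trough for that point is kept. Matching by time since first ribavirin dose is a useful comparison, but the protocol does not state it as an aim.
- **The omitted days threaten the cross-arm analysis.** That analysis uses day 28, which every list contains. Any risk to it comes from the Group C wording alone.
- **Group C will go unmeasured.** Most of the relevant text points to central assay after treatment.

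**Conclusion.** The point holds as an internal inconsistency of moderate size. The trough lists conflict, and the site instructions omit four time points that Section 5.3.1 requires. Followed alone, Appendix 5 schedules 735 of 1,015 troughs, a shortfall of 280 (27.6%), assuming 35 patients per arm, full attendance and no early stopping. The losses that matter most are the end-of-loading trough in Group A, which might be recovered from IP-10 plasma, and Group B's two priming troughs, for which Appendix 5 lists no back-up draw.

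The Group C text in the synopsis and Section 3.1, read literally, contradicts the analysis in Section 9.2.1. The probable intent is central assay with no result available during therapy, but those passages do not say so. The consequences are confined to a secondary objective and one additional SVR analysis; neither issue affects the primary HCV-RNA endpoint.

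**What to change.** 1. Reconcile the trough lists in Section 2.2 and Appendix 5 with Section 5.3.1: days 1, 3, 7, 14 and 28, weeks 8, 12 and 18, and end of treatment, plus days -27 and -21 in Group B. Check the Section 5.1 schedule against the same list.
2. Reword the Group C text in the synopsis, Section 3.1 and Appendix 3 to say that central-laboratory troughs are drawn in all arms and assayed after treatment, with no result available during therapy in Group C. This agrees with Section 1.4.1 and makes the Section 9.2.1 analysis possible.

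The cost is wording only. Section 5.3.1 already calls for these samples, and plasma is already drawn on day 14 and in week 18 for IP-10. The change should reach sites before the affected visits.
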